### Randomized allocation procedure

Allocation will be performed using a permuted block randomization procedure to help ensure a 1:1 ratio in each group. The allocation sequence will be determined using a computerized random number generator with block sizes of four participants. The allocation sequence will be concealed from the health education specialist and researchers who are enrolling potential participants with a sequential number of opaque sealed envelopes. Envelopes will be opened only after all pre-test data is collected. A researcher with no involvement in the delivery of the interventions or the screening of participants will prepare the envelopes.

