## Methods

### Trial design

We will conduct a single-center, randomized, controlled, parallel-group, rater-blinded pilot study. Thirty-five participants will be recruited and randomized into the SystemCHANGE™ intervention or a contact-control information-only intervention. Both interventions will be delivered over a 6-month period. All outcomes will be administered before the interventions and again at 3 and 6 months. The Cleveland Clinic Institutional Review Board approved this study. We will obtain informed consent from each stroke survivor that participates in the study.

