#### Treatment fidelity

To promote standard application of the interventions in both the SystemCHANGE™ group and the control group, a manual of operating procedures and lesson plans outlining each session will be provided to the health education specialist and incorporated into their training. We will use the same person to deliver the interventions in both groups to facilitate standardized delivery. The health education specialist will also be given a checklist to review and use in each session and will be monitored in-person at random intervals to determine the extent to which the lesson plans are followed. Intervention fidelity will be further monitored by tracking participant attendance, monitoring completion of homework assignments, and administering quizzes to assess participants’ understanding of the material.

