### Sample size

Our goal to recruit 35 stroke survivors is consistent with recommendations in the literature for pilot studies. Hertzog [32] has shown that samples of 10 to 20 participants per group are often adequate for evaluating feasibility in a pilot study. Furthermore, Dobkin [33] has suggested that 15 participants in each research arm are sufficient for determining whether a larger multicenter trial should be conducted.

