### Blinding

It will not be possible to blind the health education specialist or participants to group assignment. However, steps will be taken to blind the researchers who administer the outcome measures. Researchers who administer the outcome measures will be different from the researchers who conduct the screenings and deliver the interventions. Participants will be instructed not to tell the assessor of their group assignment.

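### A single fixed block size of four lets anyone who knows it and the ordered past assignments predict about 11 of 35 allocations with certainty: a possible route to selection bias, not a shown breach

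*Protocol article*

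**What the plan says.** All references are to the protocol article.

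- **Trial design** describes a "single-center, randomized, controlled, parallel-group, rater-blinded pilot study". No stratification is described anywhere, so there is one running list.
- **Randomized allocation procedure** states: "Allocation will be performed using a permuted block randomization procedure to help ensure a 1:1 ratio in each group". The sequence comes from a "computerized random number generator with block sizes of four participants"; no second size and no random variation is given. The same section conceals the sequence from the specialist and from the enrolling researchers. It uses sequential opaque sealed envelopes, prepared by a researcher uninvolved in screening or delivery and opened once baseline data are complete.
- **Blinding** states: "It will not be possible to blind the health education specialist or participants to group assignment". It separates outcome assessors from those who screen and those who deliver. It does not separate screening from delivery.
- **Treatment fidelity** adds: "We will use the same person to deliver the interventions in both groups".
- **Sample size** sets the target at 35, and **Trial status** reports that recruitment was under way when the article was submitted.

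**The concern.** The protocol wants the sequence hidden from the specialist. Yet the specialist delivers both arms unblinded and so learns who has been allocated to each, and the article prints the rule by which past allocations reveal later ones. With one list and one block size, the fourth allocation in every block is forced by the first three, and the third is forced whenever the first two agree. Opaque envelopes do nothing against that kind of deduction.

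What is at stake is entry to the trial. Screening has phone, physician and in-person stages (Participants), and the active arm meets in groups (SystemCHANGE™), so there is some room to choose when a person is brought forward. If whoever makes that choice could foresee the next allocation, the arms could differ in prognosis or motivation. The trial's main product is effect-size estimates from 35 people, about 17 or 18 per arm, so even a few steered entries could matter. The documents give no basis for saying by how much.

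**Working it through.** The article gives no predictability figure, and its sample size rests on pilot-study recommendations, so there is nothing of its own to reproduce.

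**Inputs.** Block size 4 and ratio 1:1 (Randomized allocation procedure); 35 participants (Sample size); one list (Trial design, no stratification described). 35 = 8 × 4 + 3, so there are eight full blocks and three further allocations.

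**Assumed observer.** Knows the block size, every past allocation and the order in which they were made.

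**Certain predictions.** A block has six equally likely orderings of two A and two B. An allocation is certain once one arm has used both its places. The first two allocations agree in 2 of 6 orderings.

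| Position in block | Probability that the allocation is certain | Probability that the best guess is right |
|---|---|---|
| 1 | 0 | 1/2 |
| 2 | 0 | 2/3 |
| 3 | 1/3 | 1/3 × 1 + 2/3 × 1/2 = 2/3 |
| 4 | 1 | 1 |
| Sum | 4/3 | 2.833 |

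- Per full block: (4/3)/4 = 33.3% certain.
- Over 35: 8 × 4/3 + 1/3 = 11.0 expected, and 11.0/35 = 31.4%.

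**Best guess** (always choose the under-represented arm).

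- Per full block: 2.833/4 = 70.8%.
- Over 35: 8 × 2.833 + 1.833 = 24.5 correct, and 24.5/35 = 70.0%, against 17.5 by chance.

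**Effect of varying the block size.** This was simulated with 4,000 lists of 35. The observer knows the set of sizes, each equally likely, but not their order, and updates by Bayes' rule.

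| Block sizes | Certain | Best guess right |
|---|---|---|
| 4 only | 31% | 70% |
| 4 and 6 | 5.5% | 69% |
| 2, 4 and 6 | 4.0% | 69% |
| 4, 6 and 8 | 2.3% | 67% |

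Varying the size removes most of the certainty but little of the guessing advantage.

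**Final imbalance.** With fours, eight blocks give 16 and 16, and the remaining three split 2 to 1, so the difference is 1. With sizes up to six, the list can stop three into a block of six with all three in one arm, a difference of 3.

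**The case against.** The strongest reply is that predictability is not bias. Steering needs one person, or people sharing information, who both knows the ordered history and influences entry, and the article describes no such person. It names the specialist and the enrolling researchers as separate parties. It does not say that the specialist screens or schedules, or that enrolling researchers see past allocations. Delivering both arms tells the specialist who is in each, but not necessarily the order in which envelopes were opened or where blocks begin. Most eligibility criteria are listed and checkable, a physician must confirm eligibility, and consent and baseline measurement come before the envelope is opened. A fixed block of four is also an openly stated design choice in a small pilot.

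Most of this stands, and it limits the point to a possible route. It does not close that route. Opening envelopes after baseline protects the baseline data, and independent preparation protects the list. Neither prevents foreknowledge when deciding whether or when to bring someone in. The staff separation described covers only the outcome assessors and the envelope preparer.

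A reader might also infer that an assessor who hears of one allocation can work out others. Blocks of four do not allow that. One known allocation makes another member of the same block only 2/3 likely to be in the opposite arm, and only if block membership is known. Assessors are separate staff, and participants are told not to disclose their group.

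**Conclusion.** The point holds as a weakness in a design choice. Over 35 participants, an expected 11.0 allocations (31%) are predictable with certainty and best guesses are right 70% of the time. Both figures assume knowledge of the block size, of all past allocations and of their order. That any member of staff has that knowledge and also controls entry is neither stated nor excluded.

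A reader might infer that concealment has failed or that the trial's estimate is biased. The documents support neither: they show no breach, and they provide nothing from which a bias could be sized. The change is worth making because it is cheap and any larger trial could inherit the method.

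**What to change.** For envelopes not yet opened:

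1. Have the uninvolved researcher who prepares the envelopes generate a new list with block sizes varied at random, for example 2, 4 and 6, and keep the sizes from enrolling, delivering and assessing staff.
2. Keep the running allocations from those who screen and schedule entry, and state in the protocol that these tasks are separate from delivery. The first measure leaves best-guess accuracy at about 69%, so it is not enough alone.

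The cost is a new list, new envelopes and a final imbalance of up to 3 instead of 1. That limit assumes the switch is made at the end of a block of four. A switch in mid-block could carry over a difference of up to 2, for a worst case of 2 + 3 = 5. The benefit reaches only the remaining participants, whose number the article does not give, and the simulated figures are for a whole list of 35.

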### Blinding

It will not be possible to blind the health education specialist or participants to group assignment. However, steps will be taken to blind the researchers who administer the outcome measures. Researchers who administer the outcome measures will be different from the researchers who conduct the screenings and deliver the interventions. Participants will be instructed not to tell the assessor of their group assignment.

### Statistical methods

Recruitment and data collection efforts will be managed with Research Electronic Data Capture [34]. The first step in the analysis will be to compute summary statistics, calculate outcome scores, and conduct quality control assessments. Outcome measures will be analyzed using multivariate repeated measures or one-way ANOVAs (assuming data are normally distributed). Between-subject effects will be examined by subtracting baseline scores from post-test scores and utilizing one-way MANOVA to determine whether there are significant improvements in change scores in the SystemCHANGE™ group compared to the contract-control group. Within-subject effects will be examine with repeated-measures MANOVA comparing baseline data immediately before the SystemCHANGE™ intervention to data at 3 and 6 months after receiving the SystemCHANGE™ intervention. To help minimize missing data, we will follow recommendations by Little *et al*. [35] (for example, providing monetary incentives). Effect sizes will be calculated as Cohen’s d. Feasibility and safety of the intervention will be assessed with descriptive statistics (frequencies, percentages, means, and standard deviations): number of contacted *versus* recruited subjects, reasons for non-participation, attrition (with timing and reasons), time required to train health education specialist and arrange follow-up phone calls, and adverse event monitoring (control *versus* treatment group).

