### Participants

The following methods will be used for recruitment: (1) fliers distributed at support groups; (2) referrals from clinicians; and (3) medical chart reviews. Individuals will undergo a three-part screening to confirm eligibility (phone, physician, and in-person). Subjects who meet the eligibility requirements over the phone will be mailed a demographic sheet and a release form to contact their physician. Once we confirm eligibility from their physician, arrangements will be made to re-confirm eligibility in person, obtain informed consent, collect pre-test data, and randomize participants into the SystemCHANGE™ intervention or the control intervention. Main inclusion criteria are: (1) a physician-confirmed unilateral ischemic or hemorrhagic stroke (at least 6 weeks post-stroke); (2) physician consent to participate; (3) age 30 to 75 years; (4) a BMI between 25 to 40 kg/m^2^; and (5) a stable weight for the past 4 weeks. Individuals will be excluded if they have: (1) heart disease (that is, myocardial infarction, congestive heart failure, coronary artery bypass grafting, or valve replacement during the past 3 months, serious cardiac arrhythmias, hypertrophic cardiomyopathy, and severe aortic stenosis); (2) pulmonary embolus; (3) uncontrolled resting blood pressure (that is, 140/90 mmHg) or abnormal blood pressure or heart rate response during the 6-Minute Walking Test [18] (for example, drop in systolic blood pressure of >10 mmHg from baseline), (4) uncontrolled diabetes (hospitalized in the past 6 months); (5) unable to communicate (for example, severe aphasia); (6) severe cognitive deficits (weighted score <12 on the short version of the Blessed Orientation Memory Concentration test [19]); (7) pregnancy; (8) three or more falls in the past month; (9) inability to walk 3 meters with or without a mobility device; (10) weight loss medications or medications that cause excessive weight gain (for example, corticosteroids and antipsychotic); and (11) gastric bypass surgery.

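### Between-arm effects come from unadjusted change scores although every outcome has a pre-allocation baseline; adjusting for it would sharpen the estimates for outcomes with moderate baseline correlation

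*Protocol article*

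**What the plan says.** Statistical methods first names the general approach: "Outcome measures will be analyzed using multivariate repeated measures or one-way ANOVAs (assuming data are normally distributed". It then specifies the comparison of the arms: "Between-subject effects will be examined by subtracting baseline scores from post-test scores and utilizing one-way MANOVA". Effect sizes follow from this: "Effect sizes will be calculated as Cohen’s d". None of these models carries a baseline covariate, and baseline adjustment is mentioned nowhere else in the article.

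The data needed for adjustment are already planned. Trial design states: "All outcomes will be administered before the interventions and again at 3 and 6 months". Randomized allocation procedure adds: "Envelopes will be opened only after all pre-test data is collected". Each outcome's baseline is therefore a true pre-randomisation covariate.

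On size and balance, Trial design says "Thirty-five participants will be recruited and randomized into the SystemCHANGE™ intervention or a contact-control information-only intervention", and the allocation section says "Allocation will be performed using a permuted block randomization procedure to help ensure a 1:1 ratio in each group". Blocks have four participants, and no stratification on baseline function or weight is described.

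**The concern.** A change score fixes the slope of follow-up on baseline at 1. With equal variances and a correlation below 1, the true slope is below 1. An arm that by chance starts worse then tends to show the larger improvement, through regression to the mean. With about 17 participants per arm and no stratification on baseline, noticeable chance differences are likely on some of the many outcomes.

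This matters because the Background and Discussion present effect-size estimates, on weight and on patient-reported and objective function, as a main product of the pilot and as input to a larger trial. An avoidable loss of precision falls directly on that product. The method is stated outright, so an analysis plan faithful to the article would inherit it.

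**Working it through.** **Inputs from the article.** N = 35, allocated 1:1 in blocks of four. Eight full blocks give 16 and 16, and the three remaining places split 2:1, hence 18 versus 17. Outcomes are measured at baseline, 3 and 6 months.

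**Inputs assumed.** The article gives no baseline-to-follow-up correlation (rho), SD, alpha or power. I take rho from 0.3 to 0.98, equal baseline and follow-up variance, and normal data. The calculation is for one outcome at one follow-up time.

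**The plan's own figure.** The 35 rests on pilot rules of thumb: 10 to 20 per group (20 to 40 in total) and 15 per arm (30). It fits both. There is no power calculation to reproduce.

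**Step 1, precision.** In units of the outcome variance, the per-participant variance is:

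- change score: 2(1 − rho)
- baseline-adjusted: 1 − rho²
- large-sample ratio: (1 − rho²) / [2(1 − rho)] = (1 + rho)/2

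Estimating the slope multiplies the adjusted variance by about 1 + 1/(N − 4) = 1 + 1/31 = 1.032. The equivalent N is 35 divided by the resulting ratio: the number of participants that the change-score analysis would need for the same precision.

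| rho (assumed) | (1 + rho)/2 | ratio at N = 35 | simulated ratio | equivalent N |
|---|---|---|---|---|
| 0.3 | 0.650 | 0.671 | 0.668 | 52 |
| 0.5 | 0.750 | 0.774 | 0.784 | 45 |
| 0.7 | 0.850 | 0.877 | 0.881 | 40 |
| 0.9 | 0.950 | 0.981 | 0.980 | 36 |
| 0.95 | 0.975 | 1.006 | 1.006 | 35 |
| 0.98 | 0.990 | 1.022 | 1.022 | 34 |

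The simulation used 40,000 trials of 18 versus 17 at each rho.

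**Step 2, break-even.** Setting (1 + rho)/2 × 32/31 = 1 gives rho = 62/32 − 1 = 0.9375. With 30 participants analysed it is 0.926, and the ratio at rho 0.5 is 0.779, so some dropout changes little.

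**Step 3, interval width.** Width follows the square root of the ratio: √0.774 = 0.88, √0.877 = 0.94, √0.981 = 0.99. Intervals are about 12%, 6% and 1% narrower at rho 0.5, 0.7 and 0.9.

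**Step 4, chance imbalance.** The standardised baseline difference has SE √(1/18 + 1/17) = 0.338. For any one outcome, the probability that it exceeds 0.25 SD in either direction is 0.46, and that it exceeds 0.5 SD is 0.14. An imbalance of d moves the change-score effect by −(1 − rho)d. For d = 0.338 the size of the shift is 0.17 SD at rho 0.5, 0.10 SD at 0.7 and 0.03 SD at 0.9. In the simulation the change-score estimate correlated with the baseline difference at −0.49, −0.39 and −0.22 for these three values; the adjusted estimate correlated at about zero.

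**Step 5, the two effects are one loss.** 2(1 − rho) = (1 − rho²) + (1 − rho)². The last term is the imbalance component, so steps 1 and 4 must not be added together. At rho 0.5 the change-score estimate has SE √1 × 0.338 = 0.34 SD. The 0.17 SD shift is half of that, and the confidence interval already covers it.

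**Step 6, direction under unequal variances.** With baseline SD s0 and follow-up SD s1, the change-score variance exceeds the adjusted variance, before the slope penalty, by (s0 − rho·s1)². This is never negative, so the direction does not depend on equal variances; the size does.

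**The case against.** The strongest reply is that the planned analysis is sound. Change scores in a randomised trial are unbiased over randomisations and keep the type I error, and the article makes no power claim. All of that stands. A reader might infer that the planned estimates are biased or the tests invalid; the documents do not support this. The over-correction is conditional on an observed imbalance.

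A reader might also infer that adjustment is always at least as precise. That holds only in large samples. Above a correlation of about 0.94 the slope penalty outweighs the gain at this size. Body weight, the subject of the central hypothesis, may well lie there. For it the change brings essentially nothing, or a loss of 1 to 2%.

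Nor does adjustment remove imbalance in general. It removes the linear effect of the covariate in the model.

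Time since stroke is a tempting further covariate, because entry opens at "at least 6 weeks post-stroke" and no upper limit is listed. But the article presents that list as the main criteria only, and nothing in it shows that time since stroke predicts follow-up function once baseline function is in the model. If it does not, two covariates cost about 1 + 2/30 = 1.067, and break-even falls to 2/1.067 − 1 = 0.875.

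Finally, the choice of SD for Cohen's d is a separate convention and does not follow from this point.

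**Conclusion.** The point holds as a modest, specific efficiency recommendation. For outcomes with moderate correlation, the baseline-adjusted estimate would have roughly 12 to 33% less variance (rho 0.7 down to 0.3). At rho 0.9 the gain is about 2%, and above about 0.94 there is none. The direction for moderate correlations is firm. The sizes rest on assumed correlations and equal variances, which the article does not give. The case for change rests on the pilot's purpose of supplying effect sizes and on the small cost, not on any invalidity in the plan.

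**What to change.** In Statistical methods, replace the between-arm change-score MANOVA by a separate model for each outcome. This can be an ANCOVA, or a repeated-measures model of the 3- and 6-month values, with that outcome's own baseline as covariate. Report the adjusted mean difference with its 95% confidence interval, and use that difference as the basis for the effect size. Do not add time since stroke.

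The cost is a short change of text, about one residual degree of freedom per model, and the loss of the joint multivariate test. The text should say openly that the joint test is being given up. Keeping it as a MANCOVA with every outcome's baseline would instead spend one degree of freedom per outcome, out of about 33. Sample size and visits stay as they are.

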### Obesity paradox

The relationship between nutritional status, disabling conditions, and physical function is complex and not fully understood [36,37]. A recent observational study indicated an ‘obesity paradox’ in stroke survivors [38]; that is, being either overweight or obese was associated with significantly better early and long-term survival rates compared to those with normal BMI. In a review article, Lavie *et al*. [39] noted that obesity is associated with a more favorable prognosis in at least 10 different disabling conditions, such as heart failure, advanced cancers, and HIV. Furthermore, research also indicates that weight loss is related to muscle atrophy, which can subsequently result in functional decline [40]. Thus, the existing literature raises an important question: Will weight loss adversely affect physical function or morbidity in stroke survivors?

Preliminary research in older adults and patients with heart disease or cancer suggest that modest weight loss does not adversely affect health outcomes [39]. It has also been argued that findings of the obesity paradox may be confounded by selection bias and that the use of traditional BMI categories may not be appropriate for people with disabling conditions because it does not account for muscle atrophy [36,39]. In the 2011 study showing the obesity paradox in stroke survivors, Vemmos *et al*. [38] concluded that ‘results cannot support recommendations to overweight or obese patients not to lose weight after acute ischemic stroke. On the contrary, taking into account the numerous studies that linked increased BMI with cardiovascular events, prevention of weight gain should be strongly promoted.’ Clearly, there is a need to move beyond observational studies to randomized controlled trials that can truly determine the effects of weight loss and reductions in percent body fat on health and function. We contend that weight management interventions in stroke survivors should emphasize strength training to help prevent muscle loss and use percent body fat and waist circumference as indicators of success and safety monitoring rather than body weight alone.

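### The between-arm test of improvement is a one-way MANOVA on change scores, which has no direction and uses complete cases only, so by itself it cannot establish improvement

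*Protocol article*

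**What the plan says.** All statements are from the Statistical methods section of the protocol article unless another section is named.

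- General analysis: "Outcome measures will be analyzed using multivariate repeated measures or one-way ANOVAs (assuming data are normally distributed").
- Analysed variable: "Between-subject effects will be examined by subtracting baseline scores from post-test scores".
- Between-arm test and its purpose: "utilizing one-way MANOVA to determine whether there are significant improvements in change scores in the SystemCHANGE™ group compared to the contract-control group".
- Effect measure: "Effect sizes will be calculated as Cohen’s d".
- Missing data: the article describes prevention, with the instance "for example, providing monetary incentives".
- Size (Trial design): "Thirty-five participants will be recruited and randomized into the SystemCHANGE™ intervention or a contact-control information-only intervention". Allocation is 1:1.

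The article does not say which outcomes or visits form the MANOVA vector. The end of the Background lists body weight and patient-reported and objective measures of health and function as primary. The Outcomes section names two patient-reported and two objective instruments. Follow-up is at 3 and 6 months.

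**The concern.** The question put to the test is directional: do SystemCHANGE participants improve more than controls? The test asks only whether the two mean vectors differ. In this trial the gap matters, because the Obesity paradox section itself asks: "Will weight loss adversely affect physical function or morbidity in stroke survivors". Weight improving while function worsens is therefore a pattern the trial must tell apart from benefit. A significant MANOVA does not do so.

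The method also needs a full vector per participant. Anyone lacking one component leaves the whole comparison, including the outcomes on which they were measured. The Sample size section relies on the view that "15 participants in each research arm are sufficient for determining whether a larger multicenter trial should be conducted", so there is little room to lose participants. If those who lose little weight early tend to leave, estimates from the remaining participants will flatter the intervention, and effect sizes taken from them could carry the error into the larger trial.

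**Working it through.** The article has no power calculation to reproduce. The 35 rests on pilot-study rules of thumb, and a 1:1 split gives 18 and 17.

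**Inputs.** From the article: N = 35, 1:1, two follow-up visits, and body weight plus four named instruments (five components if each contributes one score). Assumed: alpha 0.05; effects of 0.8 SD; equal correlation r between change scores, all coded so that positive means benefit; 3% missingness per follow-up measurement.

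**1. Direction.** For two arms, power comes from the noncentral F with p and N − p − 1 degrees of freedom and noncentrality

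λ = [n1·n2/(n1+n2)] × δ′Σ⁻¹δ, with n1·n2/(n1+n2) = 18 × 17/35 = 8.743.

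Under equal correlation, δ′Σ⁻¹δ = {Σδ² − r(Σδ)²/[1+(p−1)r]}/(1−r). Reversing every sign of δ leaves it unchanged, so the test cannot separate benefit from harm. For p = 5 (5 and 29 degrees of freedom, critical F 2.545) and r = 0.3:

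| True pattern | δ′Σ⁻¹δ | λ | Rejection probability |
|---|---|---|---|
| All five 0.8 better | (3.2 − 0.3×16/2.2)/0.7 = 1.455 | 12.72 | 0.705 |
| All five 0.8 worse | the same | 12.72 | 0.705 |
| One 0.8 better, one 0.8 worse | 1.28/0.7 = 1.829 | 15.99 | 0.81 |
| Two 0.8 better | (1.28 − 0.3×2.56/2.2)/0.7 = 1.330 | 11.63 | 0.66 |

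At r = 0 and 0.5 the third row is 0.64 and 0.93, and the fourth is 0.64 and 0.78. With positively correlated benefit, a conflict between two outcomes is rejected more readily than benefit on both.

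**2. Complete cases.** The share complete is 0.97^p. The Randomized allocation procedure section has envelopes opened only after pre-test data are collected, so only follow-up measurements count.

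| Vector | Components | Share | Of 35 |
|---|---|---|---|
| One outcome, two visits | 2 | 0.941 | 33 |
| Five outcomes, one visit | 5 | 0.859 | 30 |
| Five outcomes, two visits | 10 | 0.737 | 26 |

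Split evenly, 26 is 13 per arm, below the 15 the article cites; 30 is 15 per arm. If people miss whole visits rather than single measurements, the loss is close to visit attrition.

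**3. Selective dropout (illustration only).** Suppose 15% to 25% of the SystemCHANGE arm miss month 6 because of poor 3-month loss, with an odds ratio of e per SD and a correlation of 0.6 to 0.8 between visits. In simulation, completers then overstate that arm's 6-month loss by 0.08 to 0.17 SD. None of these inputs is in the article.

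**4. Power.** A two-sided t-test on one outcome at 0.8 SD has power 0.63. The MANOVA gives, at r = 0, 0.3 and 0.5:

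- five components, effect on weight only: 0.34, 0.42, 0.55;
- five components, effect on all: 0.98, 0.71, 0.55;
- one outcome at two visits, effect at both: 0.82, 0.71, 0.64.

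Power can rise or fall, depending on the vector and the effect pattern.

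**The case against.** The strongest reply is that the MANOVA is not the whole analysis. The same section names one-way ANOVAs, summary statistics and Cohen's d, each of which shows a sign per outcome. Adverse events are reported by arm, and the Risk and safety monitoring section has function, weight and muscle loss watched closely. A reader might infer that the plan has no means of showing improvement or of noticing harm. The article does not support that, and this part of the reply stands. What remains is that the sentence posing the improvement question names MANOVA alone. The ANOVAs appear as an alternative, and no rule ties them to the MANOVA result.

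A second reply is that handling of missing data may sit in an analysis plan that is not shown. That is fair, and the lack of such a rule is not the point here. The use of complete vectors follows from the method named.

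Third, a reader might infer that MANOVA always costs power. It does not: the central hypothesis expects function to improve along with weight, and under that pattern MANOVA can do better than a single-outcome test. Nor should baseline measurements be counted as cells that may go missing, which would exaggerate the loss of cases.

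Last, this is a pilot without a power-based sample size. That lowers the weight of the point, but it also favours signed estimates with intervals over an omnibus p-value.

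**Conclusion.** The point holds in a limited form. The test assigned to the improvement question has no direction, so its p-value alone cannot establish improvement. That follows from the method and needs no assumption beyond two arms and more than one component. Separately, the method uses complete cases only. This can cost participants and bias estimates, but it is not the reason the test fails to show improvement.

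The sizes are conditional. The rejection probabilities rest on alpha 0.05, 0.8 SD effects, five components and the stated correlations. The 26, 30 and 33 of 35 rest on 3% independent missingness. Because the article does not define the vector, no single figure belongs to the plan, and no general loss of power can be claimed. Severity is moderate: the trial's stated purpose is effect sizes, feasibility and safety, and the MANOVA p-value itself changes neither Cohen's d nor the feasibility counts.

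**What to change.** Replace the between-arm MANOVA with one linear mixed model for repeated measures per outcome, with terms for arm, visit, arm by visit and baseline by visit. Include every randomised participant with any follow-up, in the arm assigned. Report the signed arm difference at 3 and at 6 months with a 95% confidence interval, stating for each outcome which sign means benefit.

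The cost is a change of wording in the Statistical methods section and the use of standard software. There is no longer a single omnibus p-value across outcomes. Validity rests on data being missing at random, which is weaker than the missing-completely-at-random condition that a complete-case MANOVA needs but is still an assumption. Participants with no follow-up at all still contribute nothing.
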